## Discussion

3

Far from all individuals suffering from SAD seek and eventually find help, and far from all SAD patients respond fully to current evidence-based treatments. Low-threshold and cost-effective internet-based interventions can easily be distributed and flexibly used, representing a promising alternative to face-to-face therapy. With an optimized internet-based intervention, a broader population of people suffering from SAD can be reached at even lower costs and more effectiveness. The results of this trial are expected to improve current evidence-based treatments for SAD and increase the number of SAD patients fully responding to ICBT. If we know more about the active ingredients of CBT for SAD, we can probably identify better and briefer strategies that trigger change processes. Thus, understanding active ingredients and change mechanisms can optimize change and “build more potent, scalable, and efficient treatments” (Watkins et al., 2016, p. 2) of SAD.

We understand the use of the factorial trial as an appropriate approach to understand the differential effects of each component of SAD. Although other sophisticated approaches exist, for instance, component individual patient data meta-analysis (e.g., Furukawa et al., 2021), the component meta-analyses are based on the indirect comparisons between different trials. Thus, there is a higher likelihood that the observed differences can be attributed not to the various components but to the differences in the settings. Furthermore, the OPTIMIZE trial is planned to have a reasonably high sample size and sufficient power to detect even small changes.

Some potential limitations of this study should be addressed. The treatment dosage may vary across conditions and be lower in those conditions with fewer components. To prevent high variations in treatment dosage, the participants are encouraged by the program and by the guides to repeat the exercise. To address this potential limitation, we will control the overall treatment dosage of each participant by assessing adherence to the program. Also, there might be a spillover effect from the psychoeducation component once we briefly explain broad change principles used in established CBT treatment (i.e., cognitive restructuring, attention training and exposure). However, we do not offer any practical indication of implementing those techniques, and we do not provide any access to the exercises introduced in the relevant components.

Finally, the measure of knowledge gain (KSAD; Andersson et al., 2012; Berg et al., 2020a) might represent a limitation since the original authors have not found satisfactory reliability. We will replicate the reliability and test-retest analysis with our sample using all time points available to re-evaluate the ability of this scale to capture change in knowledge gain.

We aim to perform mediation analyses to test the hypothesized mechanisms of change. The mere statistical mediation is not enough to ascertain a mechanism of change (Kazdin, 2007). The field needs to show a solid theoretical foundation for a specific mediator and also strong statistical association, temporality (i.e. timeline shows that intervention leads to change in mediator which leads to change in outcome, not the other way around), specificity (i.e., to prove that one particular mediator is responsible for change), gradient (i.e., dose-response relationship between mediator and outcome), consistency (across studies with different samples) and coherence with other evidence, for instance, results coming from experimental studies (Kazdin, 2007). In our study, we will be able to assess temporality, specificity and the gradient of theoretically founded mechanisms of change. Although other studies will be needed to evaluate consistency and coherence with other experimental evidence, our results might move forward theoretical debates regarding the mechanisms involved in the maintenance of SAD and what works in treatments. We estimate that this trial's results will inform the treatment of social anxiety via internet interventions and inform face-to-face treatments. At a societal level, optimizing treatment and expanding the knowledge about mechanisms of change is essential because SAD is very common and one of the costliest psychiatric conditions (e.g., Fehm et al., 2005). By determining the importance of each component to the overall efficacy of CBT treatment for SAD, we will be able to inform mental health policy decisions that would probably decrease its costs and increase its effectiveness.

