**Methods:**

A total of 464 adults diagnosed with SAD will be randomized to one of 16 conditions containing combinations of the treatment components. The primary endpoint is SAD symptomatology at eight weeks. Secondary endpoints include symptoms of depression and anxiety, quality of life, and negative effects. Hypothesized change mechanisms are the increase of knowledge about SAD, the decrease of dysfunctional cognitions, the decrease of self-focused attention, and the decrease of avoidance and safety behaviors.

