### Procedures

2.6

The study procedures have been approved by the Ethics Committee of the Canton Bern (KEK Bern 2020-02952) and were registered on clinicaltrials.gov (NCT04879641). After receiving the study information and signing the informed consent, the candidates will be screened for eligibility with self-report measures. Potential participants who fulfill the inclusion criteria will be interviewed by telephone to ascertain whether they meet the criteria for SAD. After checking the inclusion criteria, the eligible participants will be randomized with equal probability to one of the 16 treatment conditions. A permuted block randomization schedule will be created using the *blockrand* package in R (Snow, 2020). The random allocation will be concealed to the investigators and done by the in-built randomization module in the REDCap software (Harris et al., 2009, Harris et al., 2019). Assessments of the primary and secondary outcomes and hypothesized mediators are taken at (1) baseline (pre-treatment), (2) at four weeks after randomization (mid-treatment), (3) eight weeks after randomization (post-treatment), and (4) at six months after randomization (follow-up).

As shown in Table 1, all conditions contain at least one component of ICBT for SAD, except for condition number 1, which is a wait-list control group. For ethical reasons, participants randomly assigned to the wait-list control group will receive the full treatment (i.e., condition 16) after the post-assessment. Participants randomized to one of the active treatment conditions can use the full treatment after the follow-up assessment (Fig. 1).

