##### Knowledge of SAD test (KSAD; Andersson et al., 2012; Berg et al., 2020a)

2.7.3.1

The KSAD assesses basic knowledge around the condition of SAD and its treatment. It includes 11 questions, each with one correct answer (out of three possible choices). In addition, each response is rated in terms of how confident the participant is about the response with three response options (Guessing, Pretty Certain, Confident). A higher score indicates more knowledge. Questions cover the content of the psychoeducation component of the Shyne program (e.g., the definition of SAD, general principles of CBT, safety behaviors, avoidance, negative automatic thoughts, attentional shift, exposure). Scores of knowledge of SAD are calculated in two ways: (a) a total score based on the total number of correct answers and (b) a weighted total score in which certainty of answers was factored in. Reliability analyses showed a low Cronbach's alpha of α  =  0.40 for the raw scores, a high Cronbach's alpha of α  =  0.86 for the certainty ratings, and an alpha of α  =  0.56 for the weighted scores (Andersson et al., 2012).

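### KSAD test-retest over all time points in the trial sample confounds reliability with intended knowledge change, and cannot show whether the scale captures change

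*Protocol article*

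**What the plan says.** The limitations part of the protocol article's Discussion concedes that for KSAD "the original authors have not found satisfactory reliability". The remedy it commits to is: "We will replicate the reliability and test-retest analysis with our sample using all time points available". The purpose follows in the same sentence: "to re-evaluate the ability of this scale to capture change in knowledge gain". No coefficient is named, and nothing limits the analysis to certain conditions or to an interval without teaching.

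Other sections set the context:

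- Section 2.7.3.1 gives the published internal consistency: "Reliability analyses showed a low Cronbach's alpha of α = 0.40 for the raw scores", with 0.56 for the weighted scores and 0.86 for the certainty ratings. It gives no test-retest figure.
- The same section says of the items: "Questions cover the content of the psychoeducation component of the Shyne program".
- The Abstract (Methods) says: "Hypothesized change mechanisms are the increase of knowledge about SAD".
- Section 2.4 says that each component also opens with a little teaching of its own.
- Section 2.6 and Table 2 place KSAD at baseline, 4 weeks, 8 weeks and 6 months.
- Section 2.6 adds that "participants randomly assigned to the wait-list control group will receive the full treatment (i.e., condition 16) after the post-assessment".

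**The concern.** A test-retest coefficient can be read as reliability only if true scores hold still, or at least keep their relative positions, between occasions. Every KSAD interval in this trial falls within or after treatment. Half the sample receives a module on the very content tested, most of the rest receive brief teaching on neighbouring topics, and one condition is untreated to week 8 and then gets everything. Differences between occasions therefore contain real and uneven learning as well as error.

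The second difficulty is the purpose. Stability and responsiveness are different properties. A scale that nobody's learning moves can be very stable, while a scale that tracks uneven learning can correlate less well with its own baseline. The planned index does not answer the stated question, whichever way it is biased.

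At stake is how the knowledge pathway is read. Knowledge is the mechanism that the psychoeducation component most directly targets, its instrument is the weakest documented of the mediator measures, and this check is the protocol's stated response to that weakness.

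**Working it through.** The document gives no test-retest coefficient, so there is no figure to reproduce. What can be checked is how intended change would move one.

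**Inputs from the document.** Psychoeducation is present in 8 of 16 conditions of 29, so 8 × 29 = 232 participants have it and 232 do not (sections 2.1 and 2.8). Condition 1 has 29 participants and is untreated only to week 8 (section 2.6). Planned dropout is 20% (section 2.8).

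**Assumptions, not in the document.** Baseline KSAD has variance 1. The correlation without true change is ρ, tried at 0.56 and 0.70; 0.56 borrows the weighted-score alpha, which is internal consistency, so it is only a plausible value. The psychoeducation half gains d SD on average, with between-person SD of gain h independent of baseline. The other half does not change.

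**Baseline to post, all participants pooled.** Post variance is 1 + d²/4 + h²/2, and the covariance with baseline stays ρ, so

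r = ρ / √(1 + d²/4 + h²/2).

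| d | h | Divisor | r if ρ = 0.56 | r if ρ = 0.70 | Loss |
|---|---|---|---|---|---|
| 0.5 | 0 | √1.0625 = 1.031 | 0.54 | 0.68 | 3% |
| 0.8 | 0 | √1.16 = 1.077 | 0.52 | 0.65 | 7% |
| 0.5 | 0.5 | √1.1875 = 1.090 | 0.51 | 0.64 | 8% |
| 1.2 | 0 | √1.36 = 1.166 | 0.48 | 0.60 | 14% |
| 1.2 | 0.8 | √1.68 = 1.296 | 0.43 | 0.54 | 23% |
| 1.0 | 1.0 | √1.75 = 1.323 | 0.42 | 0.53 | 24% |

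**Post to follow-up, gains kept.** The gain now counts as stable between-person variance:

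r = (ρ + d²/4 + h²/2) / (1 + d²/4 + h²/2).

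- d = 0.8, h = 0: (0.56 + 0.16)/1.16 = 0.62; with ρ = 0.70, 0.86/1.16 = 0.74.
- d = 1.2, h = 0.8: (0.56 + 0.68)/1.68 = 0.74; with ρ = 0.70, 1.38/1.68 = 0.82.

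This leaves out the wait-list crossover, which affects 29 of 464 participants.

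**All four occasions together.** A simulation of 400,000 subjects, with half the gain reached at mid-treatment, d up to 1.2 and h up to 0.8, gave:

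| ρ | Consistency ICC | Absolute-agreement ICC |
|---|---|---|
| 0.56 | 0.56 to 0.57 | 0.53 to 0.56 |
| 0.70 | 0.67 to 0.70 | 0.63 to 0.70 |

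The upward and downward effects partly cancel. At more extreme ρ the shift is larger: the consistency ICC rises to 0.45 at ρ = 0.40, and the absolute-agreement ICC falls to 0.74 at ρ = 0.86.

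**A uniform gain in everyone.** The Pearson correlation is unchanged (0.56 stays 0.56). The two-occasion absolute-agreement ICC becomes ρ/(1 + d²/2): 0.56/1.125 = 0.50 at d = 0.5 and 0.56/1.72 = 0.33 at d = 1.2.

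**Precision where knowledge should be stable.** Fisher-z 95% intervals, tanh(atanh r ± 1.96/√(n − 3)), at r = 0.56:

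- n = 29: 0.24 to 0.77.
- n ≈ 23 (29 × 0.8): 0.19 to 0.79.
- n = 232 (all psychoeducation-absent conditions, before dropout): 0.46 to 0.64.

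**The case against.** A reader might infer that a working programme is bound to make KSAD look unreliable. The documents do not support that. A uniform gain leaves a Pearson correlation where it was, post-to-follow-up correlations go up when gains persist, and a four-occasion ICC may hardly move. A larger loss, 13% to 33% at d and h between 0.5 and 1, appears if gains are taken to vary between people in every condition (h² in place of h²/2). That charges the variation to the untreated wait-list too, and nothing in the document fixes it.

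A reader might also infer that the knowledge mediation analysis depends on this check. It does not: section 2.9 plans the mediation without conditions, and no rule drops or reinterprets KSAD on the strength of a coefficient.

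It can fairly be said that the Discussion names neither the coefficient nor any pooling across conditions, that its wording is compatible with results by interval or by condition, and that the intention to replicate points to a published procedure not shown here. Such detail may sit in a fuller plan. The sentence also covers internal consistency, which can be computed at each occasion and is not shown to be biased.

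These points limit the direction and size of the criticism. They do not remove it. The article itself fixes the sample, the time points and the purpose, and no choice of coefficient turns a stability index over teaching intervals into a measure of responsiveness.

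**Conclusion.** The point holds as a minor one. As worded, the KSAD test-retest analysis mixes measurement error with intended, uneven change, and it is aimed at a question that it cannot answer. The bias has no single direction. Baseline-to-post correlations fall by about 3% to 24% in the scenarios tried, post-to-follow-up correlations rise if gains are kept, and four-occasion ICCs shift little at ρ of 0.56 to 0.70. All of these sizes depend on assumed ρ, d and h, and on gains being confined to the psychoeducation half. The primary analysis is not touched. What is exposed is interpretation: from the pooled coefficient alone, a reader could not tell a poor scale from a component that works.

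**What to change.** Replace the sentence in the Discussion with three statements.

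1. Test-retest reliability of KSAD will be estimated in condition 1 from baseline to week 8 only, leaving out follow-up, with the coefficient named and its 95% confidence interval given.
2. As support, within-condition (condition-adjusted) correlations over the same period will be reported for the psychoeducation-absent conditions, noting that all of these except condition 1 still receive brief psychoeducation with their components.
3. The ability to capture change will be judged separately, by the standardised psychoeducation present-versus-absent difference in KSAD gain.

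Internal consistency can still be reported at every time point.

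The cost is wording only, since all the data are already planned. The downside is low precision in condition 1: with 23 to 29 participants the interval will not separate poor from good reliability, and the report should say so. The psychoeducation-absent conditions give a narrower interval at the price of some teaching effect.
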